**Methods:**

A descriptive longitudinal study design will be used. The study will include women who underwent fistula repair between 2012 and 2015 at 3 fistula repair sites supported by the Fistula Care Project in Guinea (Kissidougou Prefectoral Hospital, Labé Regional Hospital and Jean Paul II Hospital of Conakry).

Participants giving an informed consent after a home visit by the Fistula Counsellors will be interviewed for enrolment at least 3 months after hospital discharge The study enrolment period is January 1, 2012 − June 30, 2015. Participants will be followed-up until June 30, 2016 for a maximum follow up period of 48 months. The sample size is estimated at 364 women.

The cumulative incidence rates of fistula recurrence and pregnancy post-repair will be calculated using Kaplan-Meier methods and the risk factor analyses will be performed using adjusted Cox regression. The outcomes of pregnancy will be analysed using proportions, the Pearson’s Chi Square (*χ*2) and a logistic regression with associations reported as risk ratios with 95 % confidence intervals. All analyses will be done using STATA version 13 (STATA Corporation, College Station, TX, USA) with a level of significance set at *P* < 0.05.

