**Fig. 1 Fig1:**
[figure not shown]
Study flow chart

The primary outcome is the incidence rate of the recurrence of fistula. For the purpose of this study, recurrence of fistula includes the breakdown of a repaired fistula or the occurrence of a new fistula in study participants. At the study sites, the closure of fistula was determined at hospital discharge by a pelvic exam using a dye test. During follow-up visits, women will first be asked about current medical status using the question “does the woman have continuous and uncontrolled leakage of urine?”. If the answer is “YES” then women will be scheduled for a pelvic exam with a dye test for confirmation, at the nearest health facility (health centre or health post). This question is always used at EngenderHealth supported sites to assess women at reception, before further pelvic exam. In addition, the presence of “continuous and uncontrolled leakage of urine” is commonly used as a screening question for fistula in circumstances in which a pelvic exam is not possible (e.g. Demographic and Helath Surveys, DHS); it differentiates between fistula and other forms of incontinence, which are unlikely to be continuous and uncontrolled. In some cases, it might not be feasible to perform the dye test if for instance the woman refuses to go to a health facility. This might lead to a misclassification which can bias the estimate towards a null. However, misclassification is unlikely, since women with continued urinary leakage are eager to report their experiences in order for the condition to be rectified.

The secondary outcomes include pregnancy and pregnancy and outcomes (miscarriage or abortion or term pregnancy). Pregnancy and pregnancy outcomes will be documented by a positive pregnancy test from discharge (done at recruitment or during follow-up visit or given at any time by a result from medical records such as antenatal (ANC) card) or by a self-reporting corroborated by 2 witnesses. Maternal status at delivery and mode of delivery (dead or alive; caesarean section or normal delivery; no complication or any complication) will be assessed by looking at the ANC & Delivery card or hospital records or self-reporting. Child outcome at delivery (stillbirth, neonatal death or alive) will be assessed by looking at the ANC & Delivery card or hospital records or self-reporting corroborated by 2 witnesses.

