### Sample size calculation

For the estimation of the incidence rate of the recurrence of fistula, we used the 2-Sided Confidence Intervals for 1 Proportion Confidence Interval Formula [31]. Using the existing data [19] and considering a +/- 2 % margin of error and 95 % confidence interval, we estimate the sample size of the cohort to be 280. We anticipate 20 % loss to follow-up and 10 % refusal rate and accordingly increase the sample size to 364. The same formula provides an estimation of the sample size for the incidence rate of pregnancy [31]. If we estimate the rate of pregnancy to be around 20 % at 24 months’ follow-up among successfully repaired women [20], a sample size of 264 women produces a 2-sided 95 % confidence interval with 10 % precision. Therefore, the sample size of 364 women will be sufficient to describe the objective on pregnancy and its outcomes.

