### Participants’ recruitment and follow-up

All women who underwent successful repair of OF from January 1, 2012 to June 30, 2015 at the 3 study sites are eligible for inclusion in study. However, only women with a unique obstetric fistula that was closed at discharge, as measured by a dye test, who provide written informed consent, reside in Guinea and agree with follow-up visits will be included in the study (Fig. 1). Eligible participants who refuse informed consent, who got repair outside the study sites or whose medical records are incomplete will be excluded.

Individual medical records of all women who benefited fistula repair at the 3 sites in 2012–2015 will be screened by the study team to identify those who were discharged with a close fistula (Fig. 1). After locating them through their medical records, the study team (that includes nurses called “Fistula Counsellors” who are involved in the management of women at the fistula repair sites) will contact women by home visit in their community to obtain informed consent.

Once the informed consent is obtained, the woman will be interviewed for 30 − 60 min by the study team and examined in an isolated place for inclusion in the study. Later, her medical records will be used at the fistula repair site where she got the surgery to collect her sociodemographic and clinical characteristics at the time of surgery. For all women recruited in the study, most retrospectively, new fistula or recurrence of the repaired fistula, pregnancies and their outcomes (miscarriage, stillbirth, live birth, early new-born death, maternal death, and type of maternal complication) will be documented. Health Centres and Health posts around which the study participants live will be used by the study team to perform the dye test in women who report “Continuous and uncontrolled leaking” since discharge or at the follow up visit.

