### Data analysis

Categorical data and treatment outcomes will be summarized as frequencies (%) and compared using *χ*2 or Fisher’s exact tests as appropriate. Continuous data will be presented using median (interquartile range) and compared using the Wilcoxon rank-sum test. Follow-up will be calculated from the date of hospital discharge. The date of fistula recurrence or the estimated date of pregnancy will be selected as the date of events. Patients who do not experience recurrence of fistula or pregnancy will be censored at the last follow up visit. For patients who are reported dead (by the relatives), the date of death will be used to determine their follow-up time in the study. For patients who are lost to follow up (i.e. who move from their village without any address to joint them after inclusion) the date of the last visit will be used.

Socio-demographic and clinical differences between those women who remain in the study and those who are lost-to-follow-up will be estimated to check for any imbalances at inclusion.

The incidence of fistula recurrence and that of pregnancy will be estimated using the method of cumulative incidence. The cumulative incidence rate will be compared across risk factors using Kaplan-Meier methods. Exposure variables with a *P*-value <0.2 in the univariate analysis will be included in multivariate models. Exposure variables with a *P*-value <0.2 in the univariate analysis will be included in multivariate models. A risk factor analysis will be performed using adjusted Cox regression. Associations will be reported as adjusted hazard ratios with 95 % CIs. Analysis will be done using STATA version 12 (STATA Corporation, College Station, TX, USA) with a level of significance will be set at *P* < 0.05.

For the outcomes of pregnancy (miscarriage or abortion, mother and child status at delivery), Pearson’s Chi square (*χ*2) will be used to compare proportions of these outcomes between potential exposure variables (age group, previous repair (Yes/No), fistula status at hospital discharge, use of antenatal care, delivery by caesarean section, etc.). Logistic regression analysis and models will be used and associations will be reported as risk ratios with a level of significance set at *P* = 0.05 and a 95 % confidence intervals.

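### Miscarriage/abortion is analysed as a simple proportion although pregnancies still ongoing at the fixed closing date have no outcome; completed pregnancies as denominator overstate the loss share, and all pregnancies understate it

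*Protocol article*

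**What the plan says.** All references are to the protocol article.

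- **Closing date** (Abstract, Methods): "Participants will be followed-up until June 30, 2016 for a maximum follow up period of 48 months".
- **Entry**: "All women who underwent successful repair of OF from January 1, 2012 to June 30, 2015 at the 3 study sites are eligible" (section on recruitment and follow-up of participants). The last women repaired therefore have about 12 months to closure.
- **Time origin and event date** (Data analysis): "Follow-up will be calculated from the date of hospital discharge", and for pregnancy "the estimated date of pregnancy will be selected as the date of events". A conception shortly before closure is thus a pregnancy event.
- **Outcome categories** (Study design, after Fig. 1): "miscarriage or abortion or term pregnancy". No category exists for a pregnancy still in progress.
- **Analysis of pregnancy outcomes** (Data analysis): chi-square "will be used to compare proportions of these outcomes between potential exposure variables", then logistic regression. The denominator is not given.
- **Censoring** (Data analysis): "Patients who do not experience recurrence of fistula or pregnancy will be censored at the last follow up visit". A woman who is pregnant at her last visit has already had the pregnancy event, so this rule does not reach her unknown outcome.

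The Background names miscarriage or abortion as an endpoint in its own right.

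**The concern.** A miscarriage or abortion is known within weeks or a few months of conception; a delivery takes about nine months. A calendar cut-off therefore removes future deliveries more often than losses. Among pregnancies that have ended by closure, losses are over-represented. If ongoing pregnancies are counted in the denominator as non-losses, some that will still be lost are missed and the share is too low. The direction for a given denominator follows from the timing alone; only the size needs assumptions.

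At stake is the reported level of one named secondary outcome, in a cohort that recruits until 12 months before closure and so has many recent conceptions.

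**Working it through.** **The plan's own figure.** The article gives no expected loss share. Its one figure for pregnancy is the rate: "If we estimate the rate of pregnancy to be around 20 % at 24 months" of follow-up, with 264 women for 10 % precision. An exact (Clopper-Pearson) 95 % interval at 20 % with a total width of 10 points needs n = 264, so this figure reproduces. The cohort of 364 is 280 × 1.30. The 20 % at 24 months is used below.

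**Inputs from the article.** Repairs run from January 2012 to June 2015 (42 months) and closure is 30 June 2016, so time to closure F runs from 12 to 54 months. The pregnancy rate is 20 % at 24 months.

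**Assumptions not in the article.** Repairs are spread evenly; the conception hazard is constant, starting at discharge or 6 months later; only first pregnancies count; all women are seen at closure; losses occur at 2.5 months and deliveries at 9 months; the true loss share m is 12 % or 20 %.

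**Formula.** Let C(g) be the probability of having conceived at least g months before closure. With no delay,

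h = −ln(0.8)/24 = 0.0093 per month

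C(g) = 1 − [e^(−h(12−g)) − e^(−h(54−g))] / (42h)

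- C(0) = 0.2595, or about 94 of 364 women
- C(2.5) = 0.2421
- C(9) = 0.1949, or about 71 of 364 women

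With a 6-month delay, h = −ln(0.8)/18 = 0.0124, and averaging over F gives C(0) = 0.2763, C(2.5) = 0.2536 and C(9) = 0.1923.

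Then:

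- completed = m·C(2.5) + (1 − m)·C(9)
- ongoing share = 1 − completed/C(0)
- loss share among completed = m·C(2.5)/completed
- loss share among all = m·C(2.5)/C(0)

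For m = 12 % without delay: completed = 0.12 × 0.2421 + 0.88 × 0.1949 = 0.0291 + 0.1715 = 0.2006. Ongoing is 1 − 0.2006/0.2595 = 22.7 %; the loss share is 0.0291/0.2006 = 14.5 % among completed and 0.0291/0.2595 = 11.2 % among all.

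| True loss | Delay | Ongoing at closure | Among completed | Among all |
|---|---|---|---|---|
| 12 % | none | 22.7 % | 14.5 % | 11.2 % |
| 12 % | 6 months | 27.8 % | 15.2 % | 11.0 % |
| 20 % | none | 21.3 % | 23.7 % | 18.7 % |
| 20 % | 6 months | 26.0 % | 24.8 % | 18.4 % |

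**Sensitivity.**

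- Losses spread evenly over 6 to 20 weeks: a true 12 % reads 14.3 to 15.0 % among completed, and a true 20 % about 23 to 24 %.
- All losses at 5 months, no delay: 13.6 % and 22.3 %.
- Follow-up capped at the stated 48 months (54 months is what the dates allow): 12 % without delay still reads 14.5 %.

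**Sampling error for comparison.** With 280 evaluable women, about 280 × 0.20 = 56 pregnancies are completed. The 95 % half-width is 1.96 × √(0.12 × 0.88/56) = 8.5 points at 12 % and 1.96 × √(0.20 × 0.80/56) = 10.5 points at 20 %. The bias among completed pregnancies is about 2 to 5 points.

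**Effect of restriction.** Counting only pregnancies that began at least 9 months before closure gives losses and deliveries the same C(9), so it cancels and the share equals m. The restriction keeps 0.1949/0.2595 = 75 % of pregnancies without delay and 0.1923/0.2763 = 70 % with it.

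**The case against.** **The denominator is a detail an article may leave to the full plan.** On its own, that is right: an unstated denominator would be no finding. What remains is that the article fixes the closing date, the event date, the outcome categories, the censoring rule and the test, and that under these either simple denominator gives a biased loss share. A reader might infer that the plan uses completed pregnancies and so will overstate losses; the article does not say so, and with all pregnancies the bias reverses.

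**The effect is small beside the precision.** This stands. The bias is below the 8.5 to 10.5 point half-width and mainly concerns one secondary outcome. Maternal and child status at delivery naturally has deliveries as its denominator.

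**The net direction is uncertain.** This also stands in part. Most events are ascertained retrospectively, and without a test or record the Study design section asks for self-report corroborated by two witnesses. Early losses are the least likely to be captured, which may offset part of the excess among completed pregnancies. It does not remove the mechanism.

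**Exposure comparisons.** A reader might infer that these are biased too. That is possible: with a true 15 %, losses at 2.5 months and no delay, completed pregnancies show about 17 % for repairs in the first 21 months and about 20 % for the last 21. But the exposures listed in Data analysis (age group, previous repair, status at discharge, antenatal care, caesarean section) do not include repair date, and nothing in the article links any of them to calendar time. Without such a link, the groups are shifted similarly.

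**Conclusion.** The point holds as a minor one. Under the stated design, a simple proportion of miscarriage/abortion is too high among completed pregnancies and too low among all pregnancies. Under the assumptions listed, about 21 to 28 % of pregnancies are ongoing at closure. A true 12 % reads about 14 to 15 % or about 11 %, and a true 20 % about 23 to 25 % or about 18 %, according to denominator. Only the dates and the 20 % at 24 months come from the article; the loss rates, loss timing, even accrual and constant hazard are assumed. The documents do not support a claim that the reported share will certainly be too high, that the listed exposure comparisons are distorted, or that the bias exceeds chance error.

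**What to change.** **Preferred.** Estimate loss and delivery as competing outcomes by gestational age, censoring pregnancies ongoing at the last visit. The estimated date of pregnancy is already required, so no new data collection is needed for the start date. The cost is minor programming, and no pregnancy is discarded.

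**Simpler alternative.** Restrict the miscarriage/abortion proportion and its regression to pregnancies whose estimated start is at least 40 weeks before the closing date (by 24 September 2015 for closure on 30 June 2016) or before the scheduled final visit. This costs one sentence but drops about a quarter of pregnancies for this outcome, up to about 30 % if conception starts 6 months after discharge.

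The 40 weeks should not be counted back from each woman's last contact. Data analysis ends a deceased woman's follow-up at her death, so that rule would exclude women who die in pregnancy, and maternal death is a named endpoint.

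Under either option, keep deliveries as the denominator for maternal and child status at delivery, report all maternal deaths, and state the number of pregnancies ongoing at closure.

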#### Sociodemographic and clinical characteristics

After obtaining the informed consent during the recruitment visit, a standardised questionnaire called Baseline form is used to collect the demographic and clinical characteristics of women from hospital records in the hospitals where they were discharged from. This questionnaire includes age at presentation at hospital, marital status, age at marriage, occupation, level of education, residence (rural/urban), number of pregnancies, parity, number of previous repairs, and duration of fistula. Clinical characteristics include mode of delivery related to development of the fistula, neonatal outcome at causal delivery, type of fistula (VVF, RVF or both), status of the bladder neck, nature of the fistula according to the surgeon (simple versus complex), duration of catheterization after repair, status of the operating surgeon (expatriate, local trainer, local trainee), postoperative complications, context of repair (routine repair or pooled repair) and the status of the fistula at discharge (close and continent/Close but not continent).

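### Pregnancy-outcome comparisons test age in unordered groups although age at presentation is collected; a continuous term would normally use the few pregnancies better

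*Protocol article*

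**What the plan says.** The Baseline form, described in the protocol article under Sociodemographic and clinical characteristics, records age ("This questionnaire includes age at presentation at hospital") and obstetric and repair history ("number of pregnancies, parity, number of previous repairs, and duration of fistula"). Previous repairs are therefore held as a count. The form in which age is recorded is not spelled out.

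For miscarriage or abortion and for mother and child status at delivery, the Data analysis section says that Pearson's chi-square "will be used to compare proportions of these outcomes between potential exposure variables". The bracketed examples begin "age group, previous repair (Yes/No), fistula status at hospital discharge" and end in an open *etc.*

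The next sentence reads "Logistic regression analysis and models will be used and associations will be reported as risk ratios" and gives no coding for age or previous repair. Earlier in the same section there is a general rule: "Continuous data will be presented using median (interquartile range) and compared using the Wilcoxon rank-sum test". No number of age groups, no cut-points and no power for any predictor analysis are given.

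**The concern.** The article names a coding and a test for age that discard detail it plans to collect. Grouping treats all women in one age band as alike. Pearson's chi-square then ignores the order of the bands and spends one degree of freedom for each band beyond the first. Both reduce the chance of detecting a steady change in risk with age.

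This matters more here than in a large cohort. Pregnancy outcomes are observed only in women who conceive, and adverse outcomes only in a fraction of those. Factors associated with pregnancy outcomes belong to a stated objective, and the Discussion describes the sample size as well powered, although the sample-size section covers only the precision of two rates.

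**Working it through.** **1. The plan's own figure.** The Sample size calculation section gives 264 women for a pregnancy rate of 20 % with a 95 % interval and 10 % precision. The smallest n at which the Clopper-Pearson interval at p = 0.20 has total width at most 0.10 is 264 (width 0.0999; at 263 it is 0.1001). The figure reproduces, and it concerns the rate only.

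**2. Number of pregnancies.** Rate 20 % at 24 months; cohort 280 before inflation, 364 after (same section).
- 280 × 0.20 = 56
- 364 × 0.20 = 72.8, about 73

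Follow-up may reach 48 months. Assuming a constant hazard and 33 months' mean follow-up, the proportion is 1 − 0.80^(33/24) = 0.264, which gives 74 (of 280) to 96 (of 364). With 60 pregnancies and an assumed 25 % adverse outcome, there are 60 × 0.25 = 15 adverse events.

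**3. Information kept by grouping.** Assume a normally distributed age and a linear logit. With k equal groups, the share of information kept is the between-group share of variance, (1/k) Σ m_j², where m_j is the mean of group j in standard deviations.

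| Groups | Information kept |
|---|---|
| 2 (median split) | 2/π = 0.637 |
| 3 | 0.793 |
| 4 | 0.861 |
| 5 | 0.897 |

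Unequal cuts keep less: a 30/70 split keeps 0.576 and a 20/80 split 0.490.

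**4. Effect on power.** More groups keep more information, but the unordered test pays for it in degrees of freedom. Suppose a continuous test has 0.80 power (non-central chi-square, two-sided 5 % assumed). A median split then has 0.61, three groups 0.60 on 2 df and four groups 0.57 on 3 df. A trend test on three groups has 0.70, so part of the loss comes from ignoring the order.

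**5. Simulation at the trial's scale.** Score tests, odds ratio 2 per standard deviation of age, equal groups, linear logit:

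| Pregnancies, adverse outcome | Linear | Linear + quadratic | 2 groups | 3 groups | 4 groups |
|---|---|---|---|---|---|
| 60, 25 % | 0.58–0.60 | 0.46–0.47 | 0.40 | 0.39 | 0.35 |
| 73, 20 % | 0.60 | 0.49 | 0.41 | 0.41 | 0.36–0.37 |
| 56, 25 % | 0.55 | 0.43–0.44 | 0.37 | 0.37 | 0.32 |

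Ranges are separate simulation runs. With 60 pregnancies and power 0.60 for the linear term, the gain over groups is 0.60 − 0.40 = 0.20 to 0.60 − 0.35 = 0.25. The quadratic model gains 0.47 − 0.40 = 0.07 to 0.47 − 0.35 = 0.12.

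**6. Other shapes of the age effect.**
- J shape, two assumed curves: the quadratic model has 0.58 and 0.74, the groups at most 0.26.
- Threshold at the median, odds ratio 4, 60 pregnancies: linear 0.43, quadratic 0.32, two groups 0.52.
- Threshold at the lower third, odds ratio 4, 60 pregnancies: linear 0.44, quadratic 0.38, three groups 0.44.

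**7. Previous repairs.** Assume 60 pregnancies, with 65/20/10/5 % of women having 0/1/2/3 repairs.
- Risk rises with each repair (20 % baseline risk, odds ratio 2 per repair): count 0.61, Yes/No 0.48.
- Only any against none matters (odds ratio 3.5): count 0.48, Yes/No 0.58–0.59.

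**The case against.** The strongest reply is that the article fixes little. The exposures are examples in an open list attached to a bivariate chi-square, which needs categories. The logistic model follows with no coding stated, and covariate coding is detail that an article may leave to the full plan. A rule for continuous data stands in the same section. Group comparisons for a secondary outcome are ordinary practice, and every power figure rests on assumed values.

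Much of this stands, and it rules out four stronger readings that a reader might infer.
- *Age is analysed only in groups.* The logistic coding is not stated, so this cannot be concluded. For the same reason, residual confounding by age in the adjusted model cannot be asserted.
- *Grouping costs up to a third of the power.* The 36 % loss at a median split (1 − 0.637) is a loss of information, not of power. It is also no upper limit: a 20/80 split loses 51 % of the information. Nothing in the documents fixes the split, the age distribution or the effect.
- *Yes/No for previous repair is plainly inferior.* Which coding does better depends on an unknown dose-response, as step 7 shows.
- *Grouping decides whether an effect can be seen at all.* Even the linear term has only about 0.60 power in the 60-pregnancy scenario.

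The reply does not remove the core. For the chi-square comparisons a grouped coding and an unordered test are stated, not merely left out. The Wilcoxon rule does not settle the matter either, because the section also names age group with chi-square for these outcomes and does not say which governs age.

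**Conclusion.** The point holds for age in the pregnancy-outcome comparisons. Under the assumed smooth effects, grouping age and ignoring the order costs about 20 to 25 percentage points of power against a linear term, and about 7 to 12 points against a linear-plus-quadratic model. These sizes assume 60 pregnancies, 25 % adverse outcome, odds ratio 2 per standard deviation, equal groups and a linear logit; none of these comes from the article. The advantage shrinks or reverses if the true effect is a threshold that coincides with a group boundary, and it is large if the effect is J-shaped.

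For previous repair there is no clear winner, so only a supporting analysis is justified. The Cox analyses of recurrence and of time to pregnancy do not name this coding and are not affected.

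**What to change.** In the Data analysis section, state that for the pregnancy outcomes age enters both the test of association and the logistic model as a continuous term, with a quadratic term or 3-knot spline, specified in advance, if curvature is expected. Keep age groups for descriptive tables. Show previous repairs as 0, 1, 2, 3+ as a supporting analysis next to Yes/No.

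The cost is a sentence or two, and no new data are needed. The downside is small: a smooth shape is assumed for age, and some power is lost if the true effect is a threshold that matches a group cut.

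### One exposure list is applied to every pregnancy outcome: untimed antenatal care is a biased exposure for miscarriage, and caesarean is not defined for it

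*Protocol article*

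**What the plan says.** The Data analysis section handles all pregnancy outcomes in one sentence. It opens with "For the outcomes of pregnancy (miscarriage or abortion, mother and child status at delivery" and says that the chi-square test "will be used to compare proportions of these outcomes between potential exposure variables". The list starts with age group, previous repair and fistula status at discharge, and ends with "use of antenatal care, delivery by caesarean section, etc". Logistic regression follows, in which "associations will be reported as risk ratios with a level of significance set at *P* = 0.05". No exposure is limited to some of the outcomes, and antenatal care is not placed in time relative to the end of the pregnancy.

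The Study design section, in the text after Fig. 1, defines the terms. Its secondary outcomes are "pregnancy and outcomes (miscarriage or abortion or term pregnancy", so a loss and a term pregnancy are alternatives. Caesarean appears there only as a feature of a delivery: "Maternal status at delivery and mode of delivery (dead or alive; caesarean section or normal delivery; no complication or any complication".

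**The concern.** Two of the listed exposures do not fit miscarriage or abortion, for different reasons.

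**Antenatal care.** A woman who loses a pregnancy early may have had no chance to attend. Her lack of care is then a result of the loss and not a possible cause. Counting her as unexposed moves losses into the group without care and makes care look protective.

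**Caesarean.** A pregnancy that miscarries has no mode of delivery, so caesarean has no meaning as an exposure for that outcome.

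The antenatal care result matters more. The analysis can run without any visible fault and return a plausible estimate. Antenatal care is also something that a programme can act on, and the Discussion says the findings are meant to guide policy and planning.

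**Working it through.** **1. How many pregnancies.** The Sample size calculation assumes a "rate of pregnancy to be around 20" % at 24 months and gives 264 women. An exact (Clopper-Pearson) 95 % interval for p = 0.20 with n = 264 runs from 0.153 to 0.253, a total width of 0.10, so the 264 is reproduced. Expected pregnancies are 0.20 × 264 = 52.8, 0.20 × 280 = 56, or 0.20 × 364 = 72.8 (about 73).

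**2. Antenatal care with no true effect.** Let m be the proportion miscarrying, f the share of losses that occur before any antenatal contact, and c the coverage in all other pregnancies. The article gives none of these; all three are assumptions.

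- Risk with care: R1 = m(1 − f) / [m(1 − f) + (1 − m)]
- Risk without care: R0 = m[f + (1 − f)(1 − c)] / {m[f + (1 − f)(1 − c)] + (1 − m)(1 − c)}

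With f = 0 both equal m and the risk ratio is 1, as it should be.

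Example with m = 0.12, f = 0.85:
- R1 = 0.018 / (0.018 + 0.88) = 0.020
- c = 0.60: R0 = 0.1092 / (0.1092 + 0.352) = 0.237, ratio 0.085
- c = 0.80: R0 = 0.1056 / (0.1056 + 0.176) = 0.375, ratio 0.053

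Over m = 0.10-0.20 and c = 0.60-0.80:

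| Share of losses before any contact | Apparent risk ratio (true value 1) |
|---|---|
| 85 % | 0.05-0.10 |
| 50 % | 0.21-0.37 |
| 25 % | 0.42-0.62 |

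**3. A second check by simulation.** Assumptions: losses uniform over 5-22 weeks; first visit uniform over 8-28 weeks (60 % or 85 % would attend) or 12-32 weeks (85 %); 10-20 % miscarriage; no effect of care. The apparent risk ratio was 0.04-0.20, with p < 0.05 in 63-100 % of samples of 73 pregnancies. Among would-be attenders these timings put 1 − (14²/2)/(20 × 17) = 71 % or 1 − (10²/2)/(20 × 17) = 85 % of losses before the first visit. The simulation therefore sits at the upper end of the table's range for f.

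**4. Caesarean.** Suppose miscarriages are coded as having had no caesarean. The cell for caesarean and miscarriage is then zero whatever the data, so the risk ratio and odds ratio are 0. With that single empty cell the logistic coefficient has no finite estimate (quasi-complete separation). How the test behaves depends on the counts:

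| Pregnancies | Losses, caesarean group | Losses, other | Pearson p | Fisher p |
|---|---|---|---|---|
| 52 (6 losses; 30 % of 46 deliveries) | 0/14 | 6/38 | 0.11 | 0.17 |
| 73 (7 losses; 20 % of 66) | 0/13 | 7/60 | 0.195 | 0.339 |
| 73 (7 losses; 40 % of 66) | 0/26 | 7/47 | 0.038 | 0.046 |
| 73 (11 losses; 40 % of 62) | 0/25 | 11/48 | 0.009 | 0.012 |

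The loss and caesarean proportions are again assumptions. If miscarriages are coded as not applicable, they drop out and no such table exists.

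**The case against.** The text is a condensed article. Its list is headed as potential exposures and is left open-ended, and two of its three outcomes are explicitly at delivery. Caesarean pairs naturally with those two, and the allocation of exposures to models could sit in a fuller document. This has force for caesarean: a reader might infer that the plan commits to testing caesarean against miscarriage, but the article never says so in terms. The empty cell also depends on a coding choice that the article does not make. The reading does not rescue antenatal care, which an analyst would readily test against miscarriage and which the sentence as written includes.

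A second objection is that the size of the antenatal care bias comes from outside the documents. That is correct. A reader might take a risk ratio of 0.05-0.10 as the expected result, but that range holds only if 85 % of losses precede any contact. The direction does not depend on that figure; the size does.

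Third, an opposing bias is possible. Pregnancies are documented by test, by the antenatal card or by self-report, and early losses without any contact are the least likely to be recorded. That may offset part of the effect. It is a second distortion and not a correction, and nothing in the article allows it to be sized.

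Finally, the issue is limited to a secondary outcome with few expected events. This stands and sets the weight of the point.

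**Conclusion.** The point holds in a limited form. As written, the plan crosses miscarriage or abortion with antenatal care without timing it, which biases that comparison towards a false protective effect. The apparent risk ratio lies anywhere from about 0.05 to 0.62 across the assumptions shown, with a true value of 1, before any offset from under-recorded early losses.

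Caesarean cannot serve as an exposure for miscarriage under the article's own definitions. A reader might infer that the planned test would certainly report a strong, significant protective effect of caesarean. The documents do not support that: the zero cell needs miscarriages to be coded as no caesarean, several plausible tables are not significant at 0.05, and a term without a finite estimate is a visible failure more than a believable false finding.

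The primary outcome (fistula recurrence), its sample size and the Cox analyses are untouched. The wording should be changed, but the study's main result does not depend on it.

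**What to change.** Split the exposure list by outcome in the Data analysis section:

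- **Miscarriage or abortion:** use only exposures fixed before conception, namely age group, previous repair and fistula status at discharge.
- **Mother and child status at delivery:** use caesarean and antenatal care here only, among pregnancies that reach delivery.

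This is a change of wording and needs no new data and no change in sample size. The cost is a smaller denominator for the delivery analyses and no antenatal care estimate for miscarriage.

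If that estimate is wanted, a landmark analysis or a time-dependent exposure by gestational age would be suitable, but only if gestational age at loss and at the first visit is recorded. The article mentions an estimated date of pregnancy but does not list those two items among the data collected, so this option may not be free.
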